## Statistical analyses

Statistical analysis of all study endpoints was carried out on an intention-to-treat basis. In the event of the loss of follow-up, patients were still included in the analysis for the duration in which they are observed.

All the demographic and baseline characteristics were analyzed descriptively. Frequency tables are presented for categorical variables, while mean with SD or median with range, whichever is more appropriate, is presented for numerical variables.

A two-sample *t*-test was used to compare the CVR improvement from the baseline between the EECP group and the medical management group if the normality assumption got satisfied for the CVR improvement; otherwise, the Mann–Whitney *U*-test was used. Linear regression will be carried out for relevant covariates.

The recurrence of a cerebral ischemic event was compared by the chi-square test or Fisher's Exact test, whichever is appropriate, between the EECP group and the medical management group.

For evaluating the effect of EECP on cognitive performance, various cognitive domain scores (z-scores) were calculated.

Using the mean and SD of the baseline values of the whole sample, controlling the significant baseline characteristic factors, analysis of covariance was employed to compare the mean difference of the change scores from the baseline to follow-up of the cognitive domains and individual subtest scores between real EECP and sham-EECP patients. In addition, paired *t*-tests were conducted to compare the mean within-group difference in cognition before and after EECP treatment.

We present the baseline characteristic of the 83 patients recruited in the study (Table 1).

**Table 1 T1:** Baseline characteristics of the recruited patients (*n* = 83).

**Variable**	**Best medical therapy (*n* = 41)**	**EECP + best medical therapy (*n* = 42)**	***p*-value**
Mean age (range) in yrs	57 (27–73)	55 (26–75)	0.512
Male gender, *n* (%)	24 (58.5)	29 (69.1)	0.430
Diabetes mellitus *n* (%)	17 (41.5)	13 (30.9)	0.712
Hypertension *n* (%)	22 (53.7)	27 (64.3)	0.452
Ischemic heart disease *n* (%)	3 (7.3)	3 (7.0)	0.613
Dyslipidemia *n* (%)	9 (21.9)	11 (26.2)	0.168
TIA *n* (%)	18 (43.9)	17 (40.5)	0.382
Stroke *n* (%)	23 (56.1)	25 (59.5)	0.561
MCA stenosis *n* (%)	29 (70.7)	31 (73.8)	0.361
Intracranial ICA stenosis *n* (%)	12 (26.3)	11 (26.2)	0.571
BHI on affected side (range)	0.14 (−0.23 to 0.41)	0.08 (−0.10 to 0.51)	0.628
% Net perfusion deficit on acetazolamide challenged SPECT (range)	9 (6 to 15)	11 (6 to 27)	0.317

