## Randomization

Patients would be randomized (1:1) by picking the lot from a box, prepared in advance. The included subjects (*n* = 130) will be randomly divided into EECP plus best medical therapy (*n* = 65) and best medical therapy (*n* = 65) groups according to a random draw of lots.

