## Sample size estimates

Our previous study on the role of STA-MCA bypass in patients with inclusion criteria similar to the current proposal revealed that the surgical revascularization resulted in improving metabolic perfusion (on SPECT) by 6 points (SD 7.2) (29). This resulted in a nearly 32% absolute reduction in stroke recurrence during 27 months of follow-up. However, the bypass surgery is invasive, not applicable to all cases, and has surgery-related complications. We presume that short-term EECP would have a milder improvement in cerebral hemodynamics (at least an improvement of 4 points (SD 6.5). We expect that this improvement in cerebral hemodynamics by EECP would translate into at least a 10% absolute reduction in stroke recurrence (on top of the best medical therapy). For sample size calculation, a sample size of 60 in each group (120 in total) is sufficient to detect a mean difference of 4 units (with SD 6.5 units) in CVR improvement from the baseline between EECP and medical management group with 80% power and 5% significant level. We decided to recruit 65 patients per group (130 in total) to allow for treatment dropouts, withdrawal, and lack of follow-up.

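### The primary CVR comparison is an unadjusted test of change chosen by a normality check; a baseline-adjusted regression on SPECT CVR would be the better single primary analysis

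*Protocol article*

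**What the plan says.** The protocol article's Statistical analyses section names a two-sample t-test, "used to compare the CVR improvement from the baseline between the EECP group and the medical management group". The t-test applies "if the normality assumption got satisfied for the CVR improvement"; otherwise the Mann–Whitney test is used. One sentence then adds linear regression for relevant covariates. It does not name the covariates, does not mention baseline CVR, and does not say how the regression ranks against the t-test. Analysis of covariance appears in the same section, but only for the cognitive change scores.

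Sample size estimates is built on a t-test-like contrast: the study is sized to "detect a mean difference of 4 units (with SD 6.5 units) in CVR improvement from the baseline" between arms "with 80% power and 5% significant level". The 4-point and 6.5-point figures follow from earlier SPECT results, so the working scale is SPECT points. SPECT is done at baseline and again at Visit 2.

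Table 1 covers 83 patients (41 control, 42 EECP). Its last row gives a SPECT deficit of 9 (6 to 15) in control and 11 (6 to 27) in EECP, p = 0.317. Breath-holding index is 0.14 in control and 0.08 in EECP, p = 0.628.

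**The concern.** Patients enter because CVR is impaired, and both SPECT ranges start at 6, the plan's threshold for vasodilatory failure. In such a population, change usually depends on baseline. A comparison of raw change then carries part of any baseline difference between arms into the treatment estimate, and the planned test has no means of removing it. On both CVR measures in Table 1, the EECP arm currently starts worse.

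There is a second issue. The effect measure is not fixed in advance. If the data look normal, the result is a mean difference in points. If not, it is a rank comparison, and no estimate is named on the 4-point scale used to size the trial.

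**Working it through.** **Inputs from the documents.** Difference 4 and SD of change 6.5; 80% power and 5% level (two-sided assumed); "a sample size of 60 in each group (120 in total) is sufficient"; 65 per arm recruited, allocated 1:1; baseline SPECT deficit 9 (6 to 15) against 11 (6 to 27) in 83 of 130 patients.

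**Assumed, not in the documents.** The baseline-to-follow-up correlation r, taken as 0.3, 0.5 and 0.7, and the baseline SD.

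**1. The plan's own figure.** n per group = 2 × (1.960 + 0.842)² × 6.5² / 4² = 41.5, so 42 (43 by exact t), not 60. At 60 per group the z-approximation gives 4 / (6.5 × √(2/60)) − 1.960 = 3.371 − 1.960 = 1.411, which is 92% power. The stated 60 does not follow from its inputs, which is a separate matter. Here it shows that the unadjusted test has power to spare.

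**2. Validity over randomisations.** In 20,000 simulated null trials (60 per arm, r = 0.5, SD of change 6.5), the unadjusted change test rejected in 5.1% and the mean difference was 0.01. The planned test is unbiased overall.

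**3. Effect of a given final imbalance.** Expected shift = (1 − slope) × gap, where slope = r × SD(follow-up) / SD(baseline). With equal SDs, slope = r.

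- Gap of 2 points: (1 − r) × 2 = 1.4, 1.0 and 0.6 points for r = 0.3, 0.5 and 0.7.
- If the 47 patients outside Table 1 are balanced, the gap falls to about 2 × 83/130 = 1.3 points, and the shift to about 0.9, 0.6 and 0.4 points.

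**4. Does the equal-SD assumption fit Table 1?** It requires a baseline SD of 6.5 / √(2(1 − r)) = 5.5, 6.5 and 8.4. A control range of 6 to 15 caps that arm's SD at half the range, 4.5, or at √((9 − 6)(15 − 9)) = 4.2 if 9 is a mean. So the assumption fails for control at every r used. The EECP range is wider (cap √((11 − 6)(27 − 11)) = 8.9 if 11 is a mean), so the overall slope remains open.

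Keeping the SD of change at 6.5, SD(follow-up) solves SD(f)² − 2r × SD(b) × SD(f) + SD(b)² = 42.25. For a 2-point gap (positive favours EECP):

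| Baseline SD | r = 0.3 | r = 0.5 | r = 0.7 |
|---|---|---|---|
| Equal SDs (5.5 / 6.5 / 8.4) | +1.4 | +1.0 | +0.6 |
| 4.5 | +1.17 | +0.34 | −0.74 |
| 3.8 (illustrative) | +0.97 | +0.02 | −1.16 |

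Example, SD 3.8 and r = 0.5: SD(f) = 1.9 + √(3.61 + 27.81) = 7.51; slope = 0.5 × 7.51 / 3.8 = 0.988; shift = 0.012 × 2 = 0.02.

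**5. Precision.** Var(change) = (1 − r²) SD(f)² + (slope − 1)² SD(b)², and in large samples ANCOVA keeps only the first term, so it is never less precise. With equal SDs its variance is (1 + r)/2 of the change-score variance: 65%, 75% and 85%. With baseline SD 3.8 it is 92%, 100% and 89%.

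**6. The normality gate.** Choosing between t-test and Mann–Whitney by a Shapiro–Wilk check (6,000 null trials, 60 per arm) gave type I error of 5.4% for normal and 5.1% for skewed changes.

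**The case against.** A reader might infer from Table 1 that the planned analysis is biased towards EECP and that false positives are inflated. The documents do not support that. Randomisation makes regression to the mean equal in both arms on average, and the simulated error rate is nominal. Table 1 is an interim picture of 83 of 130 patients, so the final gap is unknown. The values 9 and 11 may be medians, since the section pairs ranges with medians and the SPECT row is not labelled a mean. Rounding alone allows a gap of about 1 to 3 points. The slope is not given, and step 4 shows that the shift could be close to zero or go against EECP. These objections stand, and they remove any claim about direction or about an inflated error rate.

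A second objection is that a regression is already planned, and that a condensed article may leave its covariates to the SAP. This stands only in part. The article does fix the test for the primary aim, and that test is unadjusted. The regression sentence neither replaces it nor commits to baseline CVR.

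Third, precision is not needed: 60 per group already gives about 92% power for the stated effect. That stands. Fourth, the normality gate does little harm to type I error, and a Hodges–Lehmann shift could accompany the rank test. That also stands, but the article names no such estimate, and the summary measure still depends on the data.

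**Conclusion.** The point holds as an improvement that should be made, not as an error that invalidates the trial. The article names an unadjusted change-score comparison for its primary aim, although baseline CVR is collected and covariance adjustment is already planned for cognition. The test is valid over randomisations, but its estimate is exposed to whatever imbalance the final sample has.

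For a 2-point gap, the shift is 0.6 to 1.4 points against a 4-point target, assuming equal SDs and r of 0.7 to 0.3. For a 1.3-point gap it is about 0.4 to 0.9. With a baseline SD of 3.8 to 4.5, the shift for a 2-point gap runs from about +1.2 to −1.2. Neither size nor sign can be settled from the documents. Adjustment removes the dependence in either direction, is in large samples never less precise, and fixes one effect measure in advance.

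**What to change.** Before Visit-2 outcomes are compared by arm, replace the t-test/Mann–Whitney sentence with a single primary analysis:

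- Linear regression (ANCOVA) of Visit-2 SPECT CVR on treatment arm and baseline SPECT CVR, stating that SPECT is the primary CVR measure because it is the scale used for sample size.
- Report the adjusted mean difference with its 95% CI, using robust or bootstrap standard errors if residuals are skewed.
- Drop the normality gate. Keep the t-test and Mann–Whitney test on change as sensitivity analyses.
- State that any regression on further covariates is supportive, and name those covariates.

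The cost is wording only. The data are already scheduled at baseline and Visit 2, and the sample size need not change.

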## Follow-up assessments

All patients would be followed up for a period of 1 year. An overview of the follow-up plan is represented in Figure 1. Briefly, the evaluations performed at visit 2 and visit 3 would be as explained as follows.

**Visit- 2** would be after 4 ± 2 months from the time of randomization. Cerebral ischemic events, if any, would be recorded. In addition to the clinical evaluation, all study participants would undergo TCD vasodilatory reserve, MRI (with ASL), acetazolamide-challenged SPECT, and a detailed neuropsychological assessment.

**Visit-3** would be after 12 ± 2 months after the randomization. In addition to the clinical evaluation, all study participants would undergo TCD vasodilatory reserve and detailed neuropsychological assessment.

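### The tests named for recurrence and for the primary CVR change cannot carry out the plan's own rule that lost patients are analysed for the time they were observed

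*Protocol article*

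**What the plan says.** All statements are in the protocol article.

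- **Statistical analyses, general rule.** All endpoints are analysed by intention to treat. For a patient lost to follow-up, "patients were still included in the analysis for the duration in which they are observed".
- **Statistical analyses, recurrence.** "The recurrence of a cerebral ischemic event was compared by the chi-square test", or by Fisher's exact test where that is more appropriate. No survival or person-time method is named.
- **Statistical analyses, primary endpoint.** Improvement in CVR from baseline is compared by a two-sample t-test or, if normality fails, by the Mann–Whitney test. Linear regression is mentioned for covariates.
- **Follow-up assessments.** Follow-up is one year for everyone. SPECT after baseline is listed only at Visit 2 (4 ± 2 months). Visit 3 "would be after 12 ± 2 months after the randomization", without SPECT.
- **Sample size estimates.** The calculation asks for "a sample size of 60 in each group (120 in total"). Then: "We decided to recruit 65 patients per group (130 in total) to allow for treatment dropouts, withdrawal, and lack of follow-up".

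**The concern.** Including a patient for the time observed describes censoring: the patient contributes to the risk set until last contact and not afterwards. A chi-square or Fisher test needs one yes/no value per patient and has no place for duration. For someone lost event-free at month 2, the analyst must choose between two options. Dropping the patient breaks the intention-to-treat statement. Counting the patient as event-free for the whole year breaks the rule about observed time. The article does not say which is meant.

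The primary test has a parallel difficulty. A patient without the Visit 2 SPECT has no change score and cannot enter a t-test or Mann–Whitney test, however long that patient was observed. As written, the test uses complete cases.

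Recurrence is the first secondary aim, and the sample size section expects an absolute reduction of at least 10 points. One arm attends 35 sessions over 7 weeks and the other attends none, so retention that differs by arm is conceivable. If it occurred, the crude proportions would show part of it as a treatment effect.

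**Working it through.** **1. The plan's own figures.** The loss allowance is (65 − 60)/65 = 7.7% per arm, and 60/(1 − 0.077) = 65, so the inflation is consistent. The base figure of 60 does not reproduce. For a difference of 4 with SD 6.5, "with 80% power and 5% significant level" (two-sided assumed), n = 2 × (1.960 + 0.842)² × 6.5²/4² = 41.5, so 42 per group; 60 per group gives 92% power. That is a separate matter on which this point does not rest. It does mean that losing 5 per arm raises a question of who is analysed rather than one of power.

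**2. Inputs for recurrence.** The control risk is 20% at 12 months, an illustration based on the Introduction's figure of more than 20% in one year for significant intracranial disease. The planned loss is 7.7% per arm, or 10 of 130 in all. The article gives no loss by arm, so every split below is an assumption. Event and loss times are taken as independent and exponential.

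**3. Formula.** With λ = −ln(1 − risk) and μ = −ln(1 − loss), both per year, the share of an arm with an observed event is

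λ/(λ + μ) × [1 − exp(−(λ + μ))].

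This is the crude proportion when lost patients count as non-events.

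**4. No true effect, 20% risk in both arms (λ = 0.2231).**

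| Loss, control / EECP | Crude control | Crude EECP | Spurious difference |
|---|---|---|---|
| 7.7% / 7.7% | 19.2% | 19.2% | 0 |
| 5% / 15% | 19.5% | 18.5% | 1.0 point |
| 0% / 15.4% (all 10 losses in one arm) | 20.0% | 18.5% | 1.5 points |
| 5% / 25% | 19.5% | 17.5% | 2.0 points |

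Example, third row, EECP: μ = −ln(0.8462) = 0.1670; 0.2231/0.3902 × (1 − 0.8 × 0.8462) = 0.572 × 0.323 = 0.185. At 30% risk, the last row gives 3.0 points.

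**5. If lost patients are dropped instead.** Divide by one minus the share lost event-free, which is μ/(λ + μ) × [1 − exp(−(λ + μ))]. In the third row that share is 0.428 × 0.323 = 0.138, and 0.185/0.862 = 21.4% against 20.0%. The error is 1.4 points in the opposite direction, so its sign depends on a choice the plan leaves open.

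**6. A true difference of 20% vs 10%, lost patients counted as non-events.** Equal 7.7% loss reads as 9.6 points. Loss of 5% control and 25% EECP reads as 10.8; the reverse reads as 7.7.

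**7. Rejection rates, 20,000 simulated trials of 65 per arm, two-sided 5%.**

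| Scenario | Chi-square | Log-rank |
|---|---|---|
| No effect, loss 5% / 25% | 5.9% | 5.2% |
| 20% vs 10%, no loss | 35.7% | 36.3% |
| 20% vs 10%, loss 7.7% / 7.7% | 33.9% | 34.9% |
| 20% vs 10%, loss 5% / 25% | 42.3% | 32.8% |
| 20% vs 10%, loss 25% / 5% | 24.9% | 35.1% |

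The log-rank test changes little with the pattern of loss; the chi-square test moves with it.

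**8. Primary endpoint.** No arithmetic is needed. CVR is read here as the SPECT measure, as the sample size section uses it. There is one post-baseline SPECT, at Visit 2, so the change score exists only for patients scanned then. The 65-to-60 allowance fits an analysis that leaves the rest out.

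**The case against.** The strongest reply is that little is at stake at the planned loss. Equal loss creates no difference under the null, and even all 10 expected losses in one arm give 1.5 points. Everyone has the same planned year of follow-up, so comparing one-year risks is a legitimate choice for a secondary aim, and log-rank adds almost no power. All of this stands, and it limits the size of the point. It does not remove the mismatch between the stated rule and the named tests.

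A second reply is that intention to treat can mean comparison as randomised, which these tests allow, and that missing-data methods are commonly left to the SAP. This also stands in large part. A patient lost after Visit 2 keeps a change score. The absence of an imputation method is therefore not the fault; the fault is that the section states a rule for lost patients that the primary test cannot follow.

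Three stronger readings are tempting and are not supported:

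- **Recurrence is in fact biased.** That needs loss or timing that differs by arm or relates to outcome, and the article shows neither. Nor does it show that patients with a recurrent event are likelier to miss the scan.
- **The Visit 3 window alone could create 5.9 points.** At a constant hazard and 20% yearly risk, 1 − 0.8^(10/12) = 17.0% and 1 − 0.8^(14/12) = 22.9%. That gap requires one whole arm seen at month 10 and the other at month 14. Both arms share the window, and it is not stated to be the horizon for counting events.
- **Power of about 35% for 20% vs 10% measures this defect.** It follows from sizing the trial on CVR, and the log-rank test has nearly the same power.

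**Conclusion.** The inconsistency is real and lies within one section: lost patients are to be analysed for the time observed, while the named tests either ignore time or need a completed Visit 2 measurement. For recurrence, the comparison can be distorted if loss or follow-up differs by arm. The size is small at the planned loss (0 to 1.5 points under the null) and about 2 points under an assumed 5% vs 25% loss, against a hoped-for 10. These figures assume a 20% 12-month risk, constant hazards and loss unrelated to outcome. Loss related to outcome was not quantified.

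For the primary endpoint, the precise statement is that patients without a Visit 2 SPECT are not in the test, although those who are can be compared as randomised. This should be corrected because the remedy is cheap and carries out the plan's own rule, not because a large bias has been shown.

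**What to change.** **Recurrence.** Analyse time from randomisation to first cerebral ischaemic event, censored at last contact. Present Kaplan–Meier curves, a log-rank test or Cox model, and the 12-month risk difference with its 95% CI. The cost is recording event and last-contact dates and slightly more analysis work; power hardly changes. Censoring still assumes that loss is unrelated to outcome, so report loss by arm.

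**Primary CVR change.** Choose one of the following as the main analysis and keep the other as sensitivity:

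- Describe it as complete-case among patients with a Visit 2 SPECT, compared as randomised, and reword the intention-to-treat and loss sentences to match.
- Add an imputation-based analysis using baseline SPECT, baseline BHI and, where available, Visit 2 BHI. The gain is limited, because BHI and SPECT are taken at the same visit and someone who misses Visit 2 will usually lack both.

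The cost here is wording, plus a modest amount of programming if imputation is added.

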### Neurocognitive assessment

Vascular cognitive impairment (VCI) is one of the major sequelae of stroke and transient ischemic attack (TIA) with negative functional impact and an elevated risk for institutionalization, dependency, and death. Post-stroke VCI or dementia was reported in 24% of patients in a recent meta-analysis (62). Similarly, highly prevalent VCI (43%) has also been reported in Singaporean patients with non-disabling ischemic stroke (63). Of this population, 40% of patients had cognitive impairment without dementia, and a further 4% were diagnosed with dementia within 6 months of the index event. Interestingly, we demonstrated the impact of STA-MCA bypass surgery on neurocognitive parameters in patients with severe steno-occlusive disease of the intracranial internal carotid artery or MCA (64). We hypothesize that by improving cerebral hemodynamics, EECP treatment would improve cerebral hemodynamics as well as cognition. We will administer cognitive measures among patients recruited in this study at the baseline and follow-up. Additionally, to evaluate whether the effects of EECP are sustained, we will assess cognitive functions 1 year after completing EECP sessions. The measures would include brief cognitive screening tests (Montreal Cognitive Assessment and Mini-Mental State Examination) as well as a 30-min protocol for neuropsychological evaluation [Symbol-Digit Modalities Test (SDMT), Trail Making Test, Controlled Oral Word Association Test, Animal Naming, and the Hopkins Verbal Learning Test-Revised]. The formal neuropsychological battery employed in this study has been validated locally for Singaporean elderly people (65).

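### The cognitive ANCOVA picks covariates by an undefined significance rule and does not name the baseline score; separately, seven Table 1 p-values are wrong, and within-arm paired t-tests cannot show an EECP effect

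*Protocol article*

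**What the plan says.** In the protocol article, Statistical analyses, the cognitive results are turned into z-scores using the baseline mean and SD of the whole sample. The arms are then compared on change from baseline, "controlling the significant baseline characteristic factors, analysis of covariance was employed to compare the mean difference of the change scores". The sentence does not list the factors, say what they must be significantly related to, or give a significance level. The baseline cognitive score is not named as a covariate.

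The same paragraph adds paired t-tests to "compare the mean within-group difference in cognition before and after EECP treatment". The battery is repeated. Under Neurocognitive assessment: "We will administer cognitive measures among patients recruited in this study at the baseline and follow-up". Under Follow-up assessments it is given at about 4 months and again at about 12 months, where "all study participants would undergo TCD vasodilatory reserve and detailed neuropsychological assessment".

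The section closes with Table 1: "We present the baseline characteristic of the 83 patients recruited in the study". It has 41 patients on best medical therapy and 42 on EECP plus best medical therapy, with a p-value on each of twelve rows. The smallest is for dyslipidemia: "9 (21.9) 11 (26.2) 0.168".

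**The concern.** Three things are at issue, all around the cognitive aim or the baseline table.

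First, the covariate rule. In a randomised trial a significant baseline difference between arms is a chance event, and its p-value carries no information on whether the factor predicts cognition. A model built that way depends on the draw. It can pass over the covariate most likely to matter, the baseline score of the same test, which the trial already collects.

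Second, the Table 1 p-values. Several rows are logically tied to each other yet carry different p-values, so the column cannot be right whichever two-sided test produced it.

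Third, the paired t-tests. A before/after gain in the EECP arm mixes any treatment effect with practice on a repeated battery and with recovery. The inclusion criteria enrol patients 3 weeks to 3 months after a stroke or TIA. A significant within-arm result is therefore no evidence that EECP works, although it is easily read that way.

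**Working it through.** **Covariate rule applied to the only baseline data shown.** The twelve printed p-values in Table 1 run from 0.168 to 0.712. At an assumed 5% level a between-arm rule selects none, and what is left is a two-group comparison of raw change. In another sample it could select something by chance. With k independent tests at 5%, P(at least one) = 1 − 0.95^k, which is 46% for k = 12. Two pairs of rows are complements, so ten are distinct, and k = 10 gives 40%.

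**What the baseline score would add.** Assume equal variance σ² at baseline and follow-up, and correlation ρ (not given in the article).
- Variance of the change score: 2σ²(1 − ρ).
- Residual variance of follow-up given baseline: σ²(1 − ρ²).
- Ratio: (1 + ρ)/2, which is 0.75 at ρ = 0.5 and 0.90 at ρ = 0.8.
- Standard-error ratio: √0.75 = 0.87 and √0.90 = 0.95, so 13% to 5% smaller.

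**Table 1 p-values.** The printed counts are used, with denominators 41 and 42. Pearson χ² = N(ad − bc)² / (product of the four margins). For TIA: 83 × (18×25 − 23×17)² / (41×42×35×48) = 83 × 59² / 2,892,960 = 0.100, so p = 0.752. All nine binary rows:

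| Row | Counts | Printed p | Pearson | Yates | Fisher |
|---|---|---|---|---|---|
| Male | 24, 29 | 0.430 | 0.319 | 0.442 | 0.366 |
| Diabetes | 17, 13 | 0.712 | 0.319 | 0.442 | 0.366 |
| Hypertension | 22, 27 | 0.452 | 0.325 | 0.447 | 0.376 |
| Ischemic heart disease | 3, 3 | 0.613 | 0.976 | 1.000 | 1.000 |
| Dyslipidemia | 9, 11 | 0.168 | 0.652 | 0.846 | 0.798 |
| TIA | 18, 17 | 0.382 | 0.752 | 0.925 | 0.826 |
| Stroke | 23, 25 | 0.561 | 0.752 | 0.925 | 0.826 |
| MCA stenosis | 29, 31 | 0.361 | 0.754 | 0.946 | 0.810 |
| Intracranial ICA stenosis | 12, 11 | 0.571 | 0.754 | 0.946 | 0.810 |

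Male and hypertension lie within about 0.012 of the Yates value. The other seven match none of the three tests. Likelihood-ratio, mid-p and Barnard tests do not rescue them either.

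Part of this needs no choice of test:
- TIA and stroke are complements in each arm (18 + 23 = 41; 17 + 25 = 42), so they must share one two-sided p-value.
- So must MCA and ICA stenosis (29 + 12 = 41; 31 + 11 = 42).
- Diabetes is the male table mirrored (41 − 24 = 17; 42 − 29 = 13), yet the two rows show 0.712 and 0.430.

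One percentage is also off: 12/41 is 29.3%, printed as 26.3.

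**Paired t-tests.** Suppose EECP does nothing and practice or recovery gives a mean gain of d SDs of the change score. The power of a two-sided 5% paired t-test follows from the noncentral t with noncentrality d√n. At n = 60 (the per-group figure in Sample size estimates) it is 12%, 33%, 63% and 97% for d = 0.1, 0.2, 0.3 and 0.5. The article gives no value for d, so this range is an assumption.

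**The case against.** The strongest reply is that this is a condensed article and covariate lists normally sit in the SAP, which is not shown. That stands as far as it goes: silence on the list is no fault, and it would be wrong to infer that the baseline score is excluded. The criticism is of the rule that is stated.

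The phrase is also ambiguous. It could mean factors significantly associated with cognition, and then the complaint about between-arm p-values would not apply. What remains is that the covariates are chosen from the trial's own data and not fixed.

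A reader might also infer that Table 1 supplies the covariates, so that its wrong p-values corrupt the cognitive model. Nothing in the article says so. Table 1 describes 83 of 130 planned patients and holds no cognitive score. That the rule selects nothing is true of that table and may not hold in the final sample.

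A reader might infer that unadjusted change scores bias the comparison through regression to the mean. In a randomised trial this acts on both arms equally in expectation. The loss is precision and correction for chance baseline imbalance.

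Finally, the paired tests are additional to the between-arm ANCOVA and leave it untouched. The article does not say they would support an efficacy claim, and its silence on alternate test forms does not show that none are used. This limits the harm to interpretation, but the tests still answer no question the trial asks.

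**Conclusion.** The point holds in three limited parts.

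1. The stated covariate rule is undefined and data-driven on either reading. Replacing it with fixed adjustment for the baseline score would reduce variance to 75% to 90% of that of the unadjusted change score, if ρ is 0.5 to 0.8 and the variances are equal. It would also correct chance baseline imbalance. The gain is modest and concerns a secondary aim; the primary CVR comparison is not affected.
2. Seven of the nine binary p-values in Table 1 are wrong, taking the printed counts as correct. It does not follow that any baseline conclusion changes: the smallest recomputed p is about 0.31 across the two-sided tests tried, and none is below 0.05. Nor are all twelve rows shown to be wrong. Age, BHI and SPECT deficit are given with ranges and no SDs and cannot be checked.
3. The within-arm paired t-tests cannot separate EECP from practice or recovery. How often they would mislead depends on a practice effect that the article does not give.

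Confidence is high for the arithmetic. It is lower for how the covariate phrase was meant. This should be changed, but it does not undermine the trial.

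**What to change.** State the cognitive model in advance: follow-up z-score regressed on arm and on the baseline z-score of the same test or domain, with age as an optional second covariate. Apply it whatever the baseline p-values show, and delete the reference to significant baseline factors.

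In Table 1, recompute the p-values or remove the column, and correct the ICA percentage.

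Replace the paired t-tests with descriptive within-arm changes for both arms, set beside the between-arm difference and its confidence interval. Base the cognitive conclusion on that difference alone.

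The cost is a few lines of analysis wording and a corrected table. Baseline scores are already collected, so no new data, visits or patients are needed.
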